## Abstract

**Background:**

Chronic musculoskeletal pain (CMP) in adolescents can influence functioning and well-being, and has negative consequences for families and society as well. According to the Fear Avoidance Model, fear of movement and pain catastrophizing can influence the occurrence and maintenance of chronic pain complaints and functional disability. Primary objective is to evaluate the effectiveness of a multimodal rehabilitation program in reducing functional disability for adolescents with CMP compared with care as usual.

**Methods/Design:**

Pragmatic multicentre parallel group randomized controlled trial. Randomization by minimization (ratio 1:1) and treatment allocation will be concealed, computer-generated and performed by an independent organization. After randomization, data collection and researchers remain blinded. Inclusion of 124 adolescents and their parents is intended. This sample size is based on a 25 % difference in group mean on the primary outcome, with α = 5 %, β = 80 % and expected 15 % loss to follow up. Study population are adolescents (12–21 years) with CMP with an indication for outpatient rehabilitation treatment in the Netherlands.

The intervention group receives a Multimodal Rehabilitation Program (MRP), a multidisciplinary outpatient individual rehabilitation program. MRP consists of 2 different treatment approaches: A graded exposure module or a combination module of graded exposure and physical training. Selection of a module depends on the needs of the patient. To both modules a parent module is added. The control group receives care as usual, which is the care currently provided in Dutch rehabilitation centres. Treatment duration varies between 7 and 16 weeks, depending on treatment allocation.

Self-reported measurements are at baseline, and at 2, 4, 10 and 12 months after start of treatment. Intention to treat analysis for between group differences on all outcome variables will be performed. Primary outcome is functional disability (Functional Disability Inventory). Secondary outcome variables are fear of pain, catastrophizing, perceived harmfulness, pain intensity, depressive symptoms, and quality of life. Total direct and indirect costs and health related quality of life will be measured. Process evaluation focuses on protocol adherence, patient centeredness and treatment expectations.

**Discussion:**

A pragmatic approach was chosen, to ensure that results obtained are most applicable to daily practice.

**Trial registration:**

Clinicaltrials.gov ID: NCT02181725 (7 February 2014).

Funded by Fonds Nuts Ohra, Stichting Vooruit, and Adelante.

## Background

Chronic pain in children and adolescents is a major health concern in the paediatric population [1–3]. Up to 25 % of Dutch schoolchildren, especially adolescents, report pain for 3 months or longer (=chronic pain) [1, 4]. Internationally, prevalence rates for musculoskeletal pain vary between 11 and 38 % [3]. Chronic musculoskeletal pain is, together with headache and abdominal pain, one of the most reported pain complaints in adolescents [1, 5]. Although a broad array of medical diagnoses is involved in adolescent pain conditions, in only 10–30 % of cases a specific medical disease explaining the pain is identified [6, 7]. Unexplained musculoskeletal pain is not self-limiting: persistence rates of pain up to 30–64 % after 4 years have been reported [5, 8, 9]. Pain during adolescence even increases the risk of having a chronic pain syndrome in adulthood [5, 10].

### The consequences of musculoskeletal pain

Most adolescents function quite well regardless of pain. Nonetheless, in approximately 40 % of the adolescents with chronic pain, pain has a disabling impact on daily functioning [11–13]. Pain can interfere with developmental, school and leisure time activities, and causes serious psychological distress. It also has an impact on the adolescent’s families. Primary caregivers report more restrictions in social life and more problems with coping with the adolescent’s pain [14–16]. In addition to the psychological burden, there is little known about the financial burden of caring for a child with chronic pain [17–19].

Although the body of evidence on adult chronic pain and different rehabilitation treatments is growing, research into adolescents who suffer from chronic pain complaints is still in its infancy. Rehabilitation care for adolescents with chronic pain differs from adult care in several ways. First, in adolescent chronic pain rehabilitation, the family system, and especially influences of the parents are important to take into account. Parental behaviour, such as protective behaviour, has been shown to influence adolescent’s response to pain. This can result in greater functional disability, higher school absence and more depressive symptoms in the children [15, 20–25]. Second, situations and activities that contribute to developing and maintaining adolescent chronic pain are not completely similar to those contributing to adult chronic pain [26, 27]. Third, in adolescents with chronic pain, prevalence rates of hypermobility (40–55 %) are higher than in healthy adolescents. Hypermobility as such is not a problem, but when hypermobility is associated with complaints, such as pain, it is called joint hypermobility syndrome (HMS) [28, 29] thereby making HMS a contributing factor in treating adolescent chronic pain [30–33].

### Theoretical framework

According to the fear avoidance model of chronic pain [34], both fear of pain/movement and catastrophic thinking about pain can lead to the development and maintenance of chronic pain problems. Simons and Kaczynski [35] studied the applicability of the fear avoidance model in the paediatric population and concluded that the model is applicable, after making some modifications to account for developmental aspects at child/adolescent age. Goubert and Simons [25] presented an interpersonal fear avoidance model of pain, in which the social context of the adolescent becomes clear.

The implications of these models for a treatment approach of adolescent CMP is that lowering fear of pain/movement and accompanying catastrophic thinking could lower avoidance behaviour and increase functional ability [34]. Moreover, the interpersonal fear avoidance model accentuates the necessity to involve the family system as part of the treatment, in a way that a context can be created in which the adolescent can change. Adding the parental influences to the fear avoidance model is an important difference between the model for adults and the model for adolescents.

### Treatment of chronic pain

Adolescent chronic pain is regarded a complex health problem that requires a multidisciplinary treatment approach from a biopsychosocial perspective [17, 36, 37]. This study focuses on multidisciplinary outpatient treatment for adolescents with CMP. Outpatient treatment currently provided to adolescents in the Netherlands is mostly based on the principles of Graded Activity (GA). There is a need for more RCT’s that investigate effectiveness of different patient (and parent) interventions in paediatric CMP [17, 22, 38]. The MRP that is investigated in this study is based on Graded Exposure therapy (GE). GE specifically aims at challenging catastrophizing thoughts and performing feared activities in order to improve functional ability of patients with chronic pain. In adults with chronic pain this treatment approach is successful [39, 40]. The Maastricht University Medical Centre (MUMC) has recently developed a multimodal rehabilitation program (MRP), aimed specifically at improving adolescent’s functional ability by reducing pain-related fear. The Multimodal Rehabilitation Program consists of 2 different treatment approaches: A graded exposure module or a combination module of graded exposure and physical training. Both approaches also include a parent module. The choice of graded exposure module or combination module depends on the needs of the patient (Table 1).

**Table 1 Tab1:** Intervention group: Multimodal Rehabilitation Program, description of the treatment

Graded Exposure module	OR	Combination module (Graded exposure and physical training)
*Phase 1 Intake and PHODA-Youth (60 min)* • Information about cognitive, behavioral and psychophysiological aspects of pain complaints • Description of family system and situation • Identification of activities that are being avoided, and accompanying cognitions *Phase 2 Education (60 min)* • Explanation of treatment rationale • Explanation of treatment • Alternative explanation for persistence of pain complaints • Personal fear avoidance model *Phase 3 Graded Exposure treatment sessions (12 × 60 min)* • Systematic exposure to fear provoking activities and movements • Behavioral experiments • Generalization and relapse prevention		*Phase 1 Intake, PHODA-Youth, and physical examination (60 min)* • Information about cognitive, behavioral and psychophysiological aspects of pain complaints • Description of family system and situation • Identification of activities that are being avoided, and accompanying cognitions • Physical examination of strength, balance and propriocepsis. *Phase 2 Education Graded Exposure and training (60 min)* • Explanation of treatment rationale • Explanation of treatment: Training and graded exposure sessions • Alternative explanation for persistence of pain problems • Explanation of physical training • Personal fear avoidance model *Phase 3 Training (16x120 min)* • Training (hydrotherapy if possible), focusing on aerobic capacity, muscle strength, core stability, propriocepsis • Homework (training exercises) *Phase 4 Graded Exposure treatment sessions (6x 60 min)* • If necessary: repetition of treatment rationale • Systematic exposure to fear provoking activities and movements • Behavioral experiments • Generalization and relapse prevention
	AND	
Parent module *Phase 1 Medical education and treatment rationale* • Explanation of treatment rationale • Explanation of treatment • Alternative explanation for persistence of pain complaints • Personal fear avoidance model for their child *Phase 2 The role of pain within the family system* • Explanation of the influence of pain on the family system and interaction between parents and child • Tools to support the child in creating and maintaining behavioral change *Phase 3 Generalization and relapse prevention* • Identifying and recognizing risky situations that can trigger relapse • Preventing relapse by making plans		

### Aims of the study

This study investigates the effectiveness of a multimodal rehabilitation program (MRP) including Graded Exposure treatment in reducing functional disability (measured with the Functional Disability Inventory on short and long term) in adolescents (12–21 years) with chronic musculoskeletal pain compared with care as usual (CAU).

Secondary aims are *a)* to compare the cost-effectiveness and cost-utility of both interventions, also during the follow-up period, an *b)* to evaluate the feasibility of working with MRP in terms of treatment fidelity and patient centeredness.

## Methods

### Study design and participants

A two group pragmatic randomized controlled trial is undertaken with adolescents with CMP, with follow-up assessment at 2, 4, 10 and 12 months after start of treatment. Adolescents will be allocated to either intervention (MRP) or control (CAU) with a ratio 1:1. Patients who receive an indication for outpatient rehabilitation treatment will be invited to participate and will be randomized to either usual care (CAU) or the intervention (MRP) after informed consent is obtained. Parents will be asked to participate as well.

Estimates for the calculation of the sample size are based on the primary outcome measure, the Functional Disability Inventory (FDI). An average FDI total score of 23 (average score obtained from adolescents that were treated at the Maastricht University Medical Centre in the year before the start of this study), a standard deviation of 9.2 and an expected mean difference between intervention and control condition of 5 points on the total FDI-score were used. A difference of 5 points equals approximately a 25 % difference in mean FDI scores between intervention and control group.

Given α = 0.05, two sided testing, a power of 80 %, and anticipating 15 % loss to follow-up, a sample size of 62 participants per trial-arm was calculated. For two trial arms, this results in a total sample size of *N* = 124.

Adolescents will be recruited from 4 centres in The Netherlands: Maastricht University Medical Centre/Adelante, Laurentius Hospital Roermond, Revant Rehabilitation centre Breda and Rijndam Rehabilitation Centre in Rotterdam. Both treatments offered are embedded in the daily care process in each treatment centre, with an inclusion period of 1.5 years. Ethical approval for this trial was granted by the Medical Ethics Committee Academic Hospital Maastricht/Maastricht University, the Netherlands, NL47323.068.13/METC13-3-062.

### Eligibility criteria

Adolescents with a treatment indication for outpatient rehabilitation care for treatment of CMP, aged between 12–21 years and with adequate Dutch literacy were eligible for inclusion. Patients will be excluded if there is a) any suspicion of a medical (orthopaedic, rheumatic or neurological) disease, that can fully explain the current level of severity of pain complaints, b) any suspicion of an (underlying) psychiatric disease that hampers rehabilitation treatment or c) pregnancy.

### Randomization and allocation concealment

Patients will be randomized by minimization after informed consent is obtained. Minimization [41] was chosen to balance treatment centre, sex and age factors within the study. To execute the randomization procedures a validated electronic randomization system (ALEA, offered by the Clinical Trial Centre Maastricht, CTCM) will be used. Randomization and treatment allocation are completely independent of the study and blinded for participants including parents and all researchers, including raters and at that moment for caregivers and the consultant in rehabilitation medicine. After treatment allocation is revealed, blinding cannot be maintained for care givers. Adolescents and parents will be kept naïve concerning the comparison between the interventions. The research team remains blinded during the course of the study. Data collection is also blinded.

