#### Intervention group

In Table 1 the elements of the three modules of the MRP are described. Graded Exposure aims to increase healthy behaviour by systematically and gradually exposing adolescents to fear provoking activities and movements. Starting point for this approach is a personal hierarchy of activities feared by the adolescent. The Photograph series of Daily Activities – Youth (PHODA-Youth) [27] is used as a standardized procedure to build these personal hierarchies. All therapists in the MRP condition received training on the principles of Graded Exposure therapy and the treatment protocols, consisting of a workshop and a 3-day training provided by skilled trainers (with 3 to >15 year experience in Graded Exposure therapy). Administration of the PHODA-Youth was part of the 3-day training.

Adolescents in the intervention condition MRP receive a graded exposure module (7 weeks) or a combination module (15 weeks) with training and graded exposure. Their parents receive a parent module (3 meetings). Adolescents with CMP receive the graded exposure module. If an adolescent is additionally identified (Brighton criteria including Beighton score, will be used [29, 32, 43]) as having pain complaints related to joint hypermobility (HMS), the combination module will be offered. All parents in the MRP condition are offered the parent module, which is organised in the evening hours.

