	The instrument has 4 themes, 1) supportive and respectful relationships, 2) Information sharing and communication, 3) Supporting independence and 4) Teen-centred service. Each item is formulated as a question, starting with ‘How much do the people who work with you…’ and then a description of a specific action or behaviour of the health care professional is given. Response options range from 1–7, with a ‘not applicable’ category added. Scale scores can be calculated as the mean of the ratings for the items in the scale.	
Satisfaction/family centeredness (Process evaluation) [59, 60]	Measure of Processes Of Care – Parent form – Short form (MPOC-P-20)	16 weeks
	20 items, scored on a scale 1–7. Consists of 5 scales, 1) Enabling and Partnership, 2) Providing General Information, 3) Providing Specific Information about the Child, 4) Coordinated and Comprehensive Care for the Child and Family and 5) Respectful and Supportive Care. Responses to each item are converted to a mean for each scale. No total score can be calculated.	
Treatment expectations of children (Process evaluation) [61]	Credibility/Expectancy Questionnaire (CEQ-Adolescent)	Baseline
	On the 11 items (5 on credibility, 6 on expectancy) can be answered on a 9-point scale from ‘totally not’ to ‘totally’. Total scores are a sum score of the individual items and ranges from 11 to 99.	
Treatment expectations parents (Process evaluation) [61]	Credibility/Expectancy Questionnaire (CEQ-Parent)	Baseline
	On the 11 items (5 on credibility, 6 on expectancy) can be answered on a 9-point scale from ‘totally not’ to ‘totally’. Total scores are a sum score of the individual items and ranges from 11 to 99.	
Joint Hypermobility Syndrome (HMS) [29, 32, 43]	Birghton Criteria	Baseline
	To identify adolescents with HMS the Brighton criteria, including a Beighton score will be used. A cut-off value of ≥5 will be used for hypermobility.	

^a^Not for all measures detailed information about reliability and validity was available

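### Hypermobility syndrome decides which MRP module a patient gets, but it is neither a minimisation factor nor a protected covariate; the likely cost is a modest loss of precision

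*Protocol article*

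**What the plan says.** The section Randomization and allocation concealment says that minimisation "was chosen to balance treatment centre, sex and age factors within the study". HMS is not listed.

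Under Intervention group, adolescents in MRP receive a graded exposure module of 7 weeks. The exception is an adolescent identified by the Brighton criteria as "having pain complaints related to joint hypermobility (HMS), the combination module will be offered". The combination module lasts 15 weeks.

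Table 3 lists HMS among the study measures at baseline: "To identify adolescents with HMS the Brighton criteria, including a Beighton score will be used". It does not restrict this to one arm. Outcome measures defines baseline as before the start of treatment and does not say whether that is also before randomisation.

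Treatment of chronic pain describes module selection differently: "The choice of graded exposure module or combination module depends on the needs of the patient". The abstract says the same.

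Under Effect evaluation, covariates for the primary outcome come from potentially important baseline imbalances, are identified by univariate regression, and are removed stepwise if not significant. HMS is not named as a covariate.

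**The concern.** The protocol treats HMS as important enough to build a separate module around it, and its background section calls HMS a contributing factor in treating adolescent pain. A baseline characteristic with that role would normally be balanced by design or held in the model. Here the allocation leaves it to chance, and the analysis rule may discard it even when the arms differ on it.

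Two things are at stake. First, if HMS is related to FDI, a chance difference in HMS share moves the unadjusted MRP versus CAU contrast. Second, a comparison by HMS status is readable only if HMS is classified the same way in both arms and without knowledge of allocation. Caregivers are unblinded once allocation is revealed, and the order of Brighton assessment and randomisation is not stated. If module choice rests on needs and not on Brighton status, the CAU patients who correspond to each module cannot be identified from baseline data.

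**Working it through.** **Inputs from the protocol.** Design: "Adolescents will be allocated to either intervention (MRP) or control (CAU) with a ratio 1:1". Sample size: "Given α = 0.05, two sided testing, a power of 80 %, and anticipating 15 % loss to follow-up", with "a standard deviation of 9.2 and an expected mean difference between intervention and control condition of 5 points". Result: "a sample size of 62 participants per trial-arm was calculated". Hypermobility prevalence is 40–55 % (The consequences of musculoskeletal pain).

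**Assumptions.** The HMS share in the trial is not stated. The 40–55 % refers to hypermobility, which the protocol distinguishes from HMS, so it serves only as a proxy; 20 % is used as a lower case. The effect of HMS on FDI is not stated and is taken as 2–5 points.

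**1. The plan's own figure.** n = 2 × (1.96 + 0.84)² × 9.2² / 5², which rounds up to 54 per arm. 54 × 1.15 = 62.1, so the stated 62 is reproduced. (Dividing by 0.85 would give 64.)

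**2. How different the modules are (Table 1).**
- Graded exposure: 60 + 60 + 12 × 60 = 840 min, or 14 h.
- Combination: 60 + 60 + 16 × 120 + 6 × 60 = 2,400 min, or 40 h, with 6 exposure sessions instead of 12.
- At the 8-week assessment the 7-week module is scheduled to be over and the 15-week module is about halfway.

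**3. Chance imbalance without HMS in the minimisation.** SD of the difference in HMS share = √(2p(1 − p)/62). The probabilities are exact, from two independent binomials with 62 per arm.

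| HMS share p | SD | 1.96 × SD | P(gap ≥ 10 points) | P(gap ≥ 20 points) |
|---|---|---|---|---|
| 20 % | 0.072 | 14.1 points | 14 % | 0.5 % |
| 40 % | 0.088 | 17.2 points | 23 % | 2 % |
| 55 % | 0.089 | 17.5 points | 24 % | 2 % |

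At 40 %, the 95 % limit corresponds to roughly 30 versus 20 HMS patients.

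**4. Effect on the FDI contrast.** Shift = gap × effect of HMS on FDI.
- At the 95 % limit: 0.172 × 2 = 0.34 up to 0.175 × 5 = 0.88, so about 0.3–0.9 points.
- At one SD with the 5-point assumption: 0.09 × 5 = 0.45 points.
- The standard error of the contrast is 9.2 × √(2/62) = 1.65, and (0.45/1.65)² ≈ 0.07. Even at the top of the assumed range, HMS imbalance makes up about 7 % of the sampling variance.

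**5. With HMS as a fourth factor.** Simulated minimisation with 124 patients, 3,000 runs per setting (assumed: four equal centres, 75 % female, two age bands, HMS independent of these, assignment probability 0.8 or 1.0). At a 40–55 % share, the mean absolute gap falls from about 7 to 1–2 points, the 95th percentile from about 18 to 3–5 points, and P(gap ≥ 10 points) from 24–25 % to at most 0.1 %.

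**6. Comparisons within HMS patients.** Power for 5 points = Φ(5 / (9.2 × √(2/m)) − 1.96), with m HMS patients per arm.
- 40 % share: m = 24.8, power 48 %.
- 55 % share: m = 34.1, power 61 %.
- With 15 % loss (52.7 per arm): 42 % and 54 %.
- A gap at the 95 % limit costs only 1–2 points more (48 to 46 %; 61 to 60 %).

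**The case against.** The strongest reply is that the trial compares MRP as a tailored package with CAU, a legitimate pragmatic contrast that the aims and discussion state openly. No module-level claim is planned. Chance imbalance on one baseline variable is random error, already contained in the total SD and the confidence interval. The covariate rule looks at baseline imbalances, so HMS could be picked up, and modelling baseline FDI would absorb part of any severity difference. All of this stands, and it limits the size of the point. It does not make the covariate rule a safeguard, because a term that can be removed stepwise is not guaranteed to stay.

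A reader might infer more than the protocol supports:
- **That the modules have no balanced control.** Table 3 does not limit HMS assessment to MRP. If it is done in both arms without knowledge of allocation, CAU patients with and without HMS are concurrent randomised comparators. Unequal numbers cost precision and do not bias a within-stratum comparison. The real limit is stratum size, which minimisation does not change.
- **That HMS is the main treatment modifier.** The protocol calls it a contributing factor and gives no treatment-by-HMS effect.
- **That large imbalance is likely.** A gap of 20 points or more has about a 2 % chance.
- **That HMS is classified with the arm known.** The order is unstated, which in a condensed article is not evidence of a fault.

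One could also read the needs wording as a loose summary of the HMS rule. That is plausible, but the two are not equivalent as written.

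**Conclusion.** The point holds as an inexpensive improvement and not as a threat to the primary result. HMS determines which of two very different programmes an MRP patient receives, yet its balance is left to chance and the stated covariate rule could drop it. A gap of 10 points or more has about a one-in-four chance at a 40–55 % share and a 14 % chance at 20 %. The resulting shift in the unadjusted contrast is about 0.3–0.9 FDI points at the 95 % limit for a 40–55 % share, and smaller in most trials.

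These sizes rest on the proxy for the HMS share and on the assumed 2–5 point effect of HMS on FDI; the protocol gives neither. The comparability of CAU patients by HMS status rests on classification in both arms, independent of allocation.

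**What to change.** - **Before randomisation:** record Brighton status (HMS yes or no) in every patient, and say so.
- **Allocation:** add HMS as a fourth minimisation factor. If enrolment is under way, it applies from the amendment date.
- **Analysis:** name HMS as a fixed covariate in the FDI model, exempt from univariate screening and stepwise removal. If enrolment is complete, make this change only, before the data are analysed.
- **Reporting:** give the arm-by-HMS estimate with its interval as secondary and exploratory, in view of the low power within strata.
- **Text:** reconcile the needs wording (abstract; Treatment of chronic pain) with the HMS rule (Intervention group), so that the corresponding CAU patients can be identified. Which rule applies is for the sponsor to settle.

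The cost is one extra field in the randomisation system and no change in sample size. The real burden is that the Brighton examination, a physical examination, must be done before allocation in all patients in every centre.
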